#### Plans for Statistical Analysis

Data will be double entered into an SPSS (IBM Corp) data set, and data analysis for the study will be performed using SPSS. Statistical analysis and reporting will be presented in line with the CONSORT (Consolidated Standards of Reporting Trials) guidelines [50]. Statistical analyses will primarily be descriptive, aiming to provide estimates related to feasibility parameters and to help inform power calculations for a future definitive trial.

For the primary outcomes of feasibility, we will calculate proportions or rates and appropriate CIs. We will consider whether a larger phase III effectiveness trial is feasible based on three potential factors: ≥25% of eligible women agree to be randomized, ≥50% of women in the intervention arm take up the intervention, or there is less than <20% attrition (women withdrawn from the study or lost to follow-up).

The secondary outcomes will be summarized using appropriate summary statistics overall and by randomization arm at each outcome time point. Normally distributed continuous variables will be summarized using the mean and SD, skewed continuous variables using the median and IQR, and categorical variables using frequencies and proportions. As the majority of the secondary outcomes are continuous and repeatedly measured, we will estimate the mean difference between the arms using linear mixed effects models with a random intercept at the participant level. The repeatedly measured outcomes will be the dependent variables, with the independent variables being trial arm, time, and a trial arm by time interaction term to extract differences at different time points. We will use analysis of covariance models where possible (ie, also include the baseline measure of the outcome as another independent variable). Appropriate 95% CIs will be calculated for the overall group and by trial arm, but as this is a feasibility study, we will not compare these statistically nor provide a *P* value for comparisons between arms. We will also not impute missing data, although fitting the mixed effects models using maximum likelihood will help account for missing data under a missing at random assumption. Some variables (eg, PHQ-9 and conversion to T2D [HbA_1c_ of 48 mmol/mol]) will also be summarized (but not analyzed) as categorical variables based on their clinical cutoffs. Smoking status and the obstetric outcomes that will only be measured once will also be summarized rather than modeled.

In terms of the process evaluation, all quantitative data including checklists, logs, and feedback surveys will be analyzed using SPSS. Data will be analyzed descriptively by calculating total numbers and percentages and mean and SD or, if the data are not normally distributed, the median and range. Qualitative data will be analyzed using thematic analysis to identify, analyze, and report patterns (themes) within the data [51].

Overall, the proportion of missing data for individual items and measures will be examined to determine the suitability of instruments and the level of burden for a future full-scale trial. As this is a feasibility study, no subgroup analyses are planned.

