### Data Collection

#### Feasibility Outcomes

The primary feasibility outcomes are to estimate the proportion of women who were randomized out of those identified from the clinical registers (study population); the proportion of women who take up the intervention out of those in the intervention arm, to be defined by measures of digital analytics (data will be collected on date of log in, time spent on each component of the app, and total time spent on the app); and the proportion of women who are withdrawn or lost to follow-up out of those randomized (ie, those who provide no primary or secondary outcome data).

The secondary feasibility outcomes are to estimate the proportion of women identified from clinical registers (study population) who give consent for screening for eligibility; the proportion of women who were randomized out of those eligible to participate; the proportion of those who completed the secondary outcomes at follow-up out of those randomized; and the number of women randomized per month overall and per month per study site.

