### Statistical Analysis

#### Sample Size

The aim is to recruit 30 women per arm, as this should be a large enough sample to estimate parameters such as the SD, which in turn can be used to estimate the sample size for an appropriately powered full-scale RCT [48]. This sample should also allow us to estimate the 95% CI for the primary feasibility outcome of the proportion randomized of those eligible, which we estimate will be approximately 10%, to a CI of within +/-8% [49]. This was calculated as:

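### The sample-size section expects about 10% of eligible women to be randomized, but the progression factor asks for at least 25% of eligible women, and the article neither reconciles the two nor keeps one denominator

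*Protocol article*

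**What the plan says.** Three sections of the protocol article bear on the recruitment proportion.

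- **Sample Size.** The target is 60 women: "The aim is to recruit 30 women per arm". The section then says this sample allows the team to "estimate the 95% CI for the primary feasibility outcome", which it names as "the proportion randomized of those eligible, which we estimate will be approximately 10" per cent, "to a CI of within +/-8" per cent. The denominator given is eligible women, and the quantity is called primary.
- **Plans for Statistical Analysis.** "We will consider whether a larger phase III effectiveness trial is feasible based on three potential factors". The first is "≥25% of eligible women agree to be randomized". The other two are uptake of at least 50% in the intervention arm and attrition below 20%. The list is joined by 'or'.
- **Feasibility Outcomes.** The primary recruitment outcome is "the proportion of women who were randomized out of those identified from the clinical registers (study population". A separate quantity, "the proportion of women who were randomized out of those eligible to participate", is listed among the secondary feasibility outcomes.

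The Randomization section adds that recruitment continues until each arm has 30 women.

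**The concern.** Both the planning value and the threshold are attached to eligible women, yet one is 10% and the other 25%. Nothing in the article explains the gap. If both are meant as written, the planned interval lies wholly below the pass mark and the study is set up to miss its own recruitment factor. The investigators would then either report a miss that their planning value already implied, or revise the threshold with the data in view.

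The sample-size text also disagrees with the outcome definitions about which recruitment proportion is primary. A reader therefore cannot tell whether the 10% is a pessimistic forecast for eligible women or a register proportion under the wrong label. These two faults need different corrections.

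**Working it through.** **Inputs.** Expected proportion 10%, 95% CI within ±8 points, 60 women (Sample Size); threshold 25% of eligible women (Plans for Statistical Analysis); stop at 30 per arm (Randomization); register and eligible denominators (Feasibility Outcomes).

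**1. Reproduce the stated precision.** The half-width for a single proportion is 1.96 × √(p(1−p)/n).
- p = 0.10, n = 60: 1.96 × √(0.09/60) = 0.076, or 7.6 points. This matches 'within ±8'.
- p = 0.10, n = 30: 10.7 points, which does not match.

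So the stated figure uses the 60 randomized women as the denominator. They are the numerator of this proportion.

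**2. Compare the planned interval with the threshold.** The upper limit is 10 + 8 = 18% as stated, or 17.6% from the formula. With 6 of 60 it is 20.1% by Wilson and 20.5% by the exact method. All lie below 25%.

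**3. Chance of meeting the factor under the stopping rule.** Recruitment ends at 60 randomized, so the observed proportion is 60/N, with N the number of eligible women by then. It is at least 25% only if N ≤ 60/0.25 = 240. That is the same as at least 60 of the first 240 eligible women being randomized: P(X ≥ 60), X ~ Binomial(240, p).

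| True proportion of eligible women | Chance of meeting the factor |
|---|---|
| 10% (planning value) | about 2e-11 |
| 18% (stated upper limit) | about 0.4% |
| 20% | about 3% |
| 25% | about 52% |
| 30% | about 96% |

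At 10%, the expected N is 60/0.10 = 600, against the 240 that the factor allows.

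**4. The register reading.** Suppose 10% is randomized/register, and f is the fraction of register women who are eligible. Then randomized/eligible = 0.10/f, and 0.10/f ≥ 0.25 requires f ≤ 0.40. The article gives no f, so a range is shown:

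| f (assumed) | Implied randomized/eligible |
|---|---|
| 0.2 | 50% |
| 0.3 | 33% |
| 0.4 | 25% |
| 0.5 | 20% |
| 0.8 | 12.5% |
| 1.0 | 10% |

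**5. Precision on the actual denominator.**
- 60/600 = 10%: 1.96 × √(0.09/600) = 2.4 points.
- 60/240 = 25%: 1.96 × √(0.25 × 0.75/240) = 5.5 points.

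**The case against.** The best defence is that the 10% is simply mislabelled. The Sample Size section attaches it to the primary feasibility outcome, and Feasibility Outcomes defines that outcome on the registers. The recruitment pathway points the same way: women are picked from the register, and consent and eligibility screening then come together. Women confirmed eligible have thus largely consented already, which makes 10% of them an oddly low forecast and 10% of register women a natural one. This stands as a plausible reading. It does not remove the fault, because Sample Size says eligible and agreement with the threshold needs an eligible fraction of at most 40% that the article never gives.

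It could also be said that agreeing to be randomized is not the same as being randomized. Allocation follows consent, eligibility confirmation and baseline assessments at one visit, so this is unlikely to explain a 2.5-fold gap.

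Two stronger inferences are tempting and are not supported:

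- **That the feasibility decision is settled before the trial starts.** The factors are described as potential and joined by 'or', so missing one does not determine progression.
- **That a 25% cut-off cannot separate feasible from infeasible recruitment.** The table in step 3 shows that it separates 20% from 30% well. A planning value below the threshold is a pessimistic forecast and does not make the rule useless.

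Tail probabilities from a fixed number of eligible women (0.0007 with 60, about 5e-26 with 600) should not be used either, because recruitment stops on the number randomized.

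**Conclusion.** The inconsistency is real and lies in the article's own figures. If 10% of eligible women is truly expected, a result as planned misses the recruitment factor almost with certainty (about 2e-11 at exactly 10%, about 0.4% even at the stated upper limit of 18%). That rests on reading Sample Size literally, treating the approximate planning value as the true rate, and stopping at 60 randomized. If the 10% belongs to the register, the conflict with 25% disappears only when at most 40% of register women are eligible. The fault is then a wrong denominator in Sample Size. The article does not settle which reading is right.

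Under either reading, the ±8 points is computed on the randomized women and not on the denominator of the proportion. The effect is confined to the planning figure, its precision and one progression factor. Allocation and outcome collection are untouched, and both proportions are already listed for reporting.

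**What to change.** State the denominator of the 10% and make Feasibility Outcomes, Sample Size and Plans for Statistical Analysis agree on it and on which recruitment proportion is primary.

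- **If the 10% is the register proportion:** correct Sample Size, state the assumed eligible fraction, and give the expected proportion of eligible women beside the 25% threshold.
- **If it is the eligible proportion:** reconcile the planning value with the threshold and justify the threshold by the recruitment rate a definitive trial needs. Recruitment began in February 2022, so the threshold should not simply be lowered to fit. Any change should be dated and recorded as made before the recruitment proportion is examined.

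In either case replace the ±8 points with the precision on the actual denominator: about ±2.4 points at 60/600, or ±5.5 points at 60/240.

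The cost is wording in three sections and one recalculated figure, with no change to trial conduct.

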#### Lifestyle

Dietary intake will be assessed using standardized multiple-pass 24-hour dietary recall for 3 days (2 weekdays and 1 weekend day) as it is considered an objective and reliable measure of change in intervention studies [36]. Clinical researchers will be trained to follow a standardized protocol, ask neutral probing questions to encourage recall of food items, and taught about different methods of food preparations and brands in different cultures. Physical activity will be measured using the Short-form International Physical Activity Questionnaire (SF-IPAQ), which comprises seven items to capture average daily time spent sitting, walking, and engaging in moderate and vigorous physical activity over the last 7 days [37]. Step count will be measured using inbuilt features of the patients’ own smartphone; the previous 7-day average will be used. Smoking status will be measured using a single item measure with response options including current smoker, previous smoker, and never smoked. Alcohol intake will be measured using the first question of the Alcohol Use Disorders Identification Test [38].

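### Baseline is a model covariate and no imputation is allowed, so a woman lacking a baseline value would leave that outcome's adjusted model; maximum likelihood does not cover this case

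*Protocol article*

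**What the plan says.** All in the protocol article, Plans for Statistical Analysis unless another section is named.

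- **Model:** "we will estimate the mean difference between the arms using linear mixed effects models with a random intercept at the participant level".
- **Role of the repeated measures:** "The repeatedly measured outcomes will be the dependent variables, with the independent variables being trial arm, time, and a trial arm by time interaction term". Baseline is therefore not one of the modelled outcomes.
- **Baseline adjustment:** "We will use analysis of covariance models where possible (ie, also include the baseline measure of the outcome as another independent variable").
- **Missing data:** "We will also not impute missing data, although fitting the mixed effects models using maximum likelihood will help account for missing data". The condition attached is that values are missing at random. The no-imputation rule makes no exception for baseline values.
- **Allocation (Randomization):** consent, eligibility, baseline assessments and the telephone request for allocation all belong to the 30-week baseline visit. Allocation is requested only after baseline assessments are complete and is looked up the same day.
- **Baseline lifestyle measures (Lifestyle, under Baseline Measures Collected Before Randomization):** dietary recall covers two weekdays and one weekend day. For step count from the woman's own phone, "the previous 7-day average will be used".
- **Reporting of missingness:** "the proportion of missing data for individual items and measures will be examined".

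**The concern.** A mixed model fitted by maximum likelihood uses whatever follow-up values a woman has, and under missing at random it allows for those she lacks. That likelihood is conditional on the covariates. Once baseline is a covariate, a missing baseline makes every row for that woman unusable for that outcome. The ban on imputation then closes the simple way of keeping her. The property the plan claims for its missing-data handling therefore does not extend to the baseline-adjusted models it plans.

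Three things would be at stake. The number of women analysed would differ by measure for a reason the plan does not state. A woman could count as retained in the attrition result, because she provided outcome data, yet be absent from an adjusted model. For step count, the women kept would be those whose phones were already recording steps at 30 weeks, since the Inclusion Criteria require a smartphone with internet but not active step recording.

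**Working it through.** **Inputs.** 60 women, 30 per arm (Sample Size). The share *m* of women without a baseline value is not given, so I assume 5% to 30%, the top end being a pessimistic case for step count. The baseline-to-follow-up correlation *r* is not given either; I assume 0.5. The plan states no figure on this point to reproduce.

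**Step 1: does the planned model drop these women?** Both model forms were fitted by maximum likelihood to simulated data (60 women, five follow-up times, complete follow-up).

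| Baselines missing | Women used, baseline as covariate | Women used, baseline as an outcome |
|---|---|---|
| 0 | 60 | 60 |
| 3 | 57 | 60 |
| 6 | 54 | 60 |

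The loss equals the number of missing baselines, and is zero when none is missing.

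**Step 2: cost in precision.** Take one follow-up time, outcome SD of 1, equal arms and baselines missing completely at random.

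- Women with baseline only: SE = sqrt[4(1 − r²) / (60(1 − m))].
- All women, missing baseline filled and flagged: the residual variance averages over both kinds of women, so SE = sqrt{4[(1 − m)(1 − r²) + m] / 60}.

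With r = 0.5, 1 − r² = 0.75:

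| m | Women used | SE, dropped | SE, all kept | Ratio |
|---|---|---|---|---|
| 0% | 60 | sqrt(3/60) = 0.224 | 0.224 | 1.00 |
| 5% | 57 | sqrt(3/57) = 0.229 | sqrt(4 × 0.7625/60) = 0.225 | 1.02 |
| 10% | 54 | sqrt(3/54) = 0.236 | sqrt(4 × 0.775/60) = 0.227 | 1.04 |
| 20% | 48 | sqrt(3/48) = 0.250 | sqrt(4 × 0.80/60) = 0.231 | 1.08 |
| 30% | 42 | sqrt(3/42) = 0.267 | sqrt(4 × 0.825/60) = 0.235 | 1.14 |

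A simulation of 6,000 trials per row, with mean fill plus indicator, gave ratios of 1.02, 1.03, 1.09 and 1.14 at 5%, 10%, 20% and 30%. Coverage of the 95% interval with the filled baseline was 94.7% to 95.2%. A separate simulation with mean fill gave 1.025, 1.047, 1.092 and 1.136.

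**Step 3: is baseline-as-outcome a safe alternative?** In a random-intercept model it forces the 30-week value to share one variance and one common correlation with the later values. Complete data were simulated with assumed correlations of 0.8 among follow-ups and 0.5 with baseline. Across three separate simulations the model reported an SE of about 0.18 for the last-visit difference, while the true SE was 0.23 to 0.25. The reported SE is thus about 21% to 28% too small (0.181/0.229 = 0.79; 0.18/0.25 = 0.72). In one of these simulations (500 trials) the nominal 95% interval covered 85% of the time. When all correlations were set to 0.5, the two models agreed. This alternative can therefore do harm even when no baseline is missing.

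**The case against.** **Completed baseline is a condition of allocation.** This is the strongest point, and it stands. If the Randomization section is followed for every measure, no randomized woman lacks a baseline and nothing is lost. A reader might infer from the missing-data rule that randomized women will be lost; the article does not support that. It supports only that they would be lost if a value were missing. The exception is plausible mainly for two measures. Recalls for two weekdays and a weekend day are hard to fit before a same-day allocation, and a 7-day step average needs history already on the phone.

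**The reporting of missing data shows nothing about baseline.** Correct. Examining missingness by item and measure is ordinary feasibility reporting and does not mean that missing baselines are expected. Nor does any section suggest that fasting samples will be missed.

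**The wording is hedged.** Likelihood is said only to help, and adjustment applies where possible. The second phrase reads most naturally as excluding outcomes without a baseline, such as the OGTT and the postnatal attachment scale. It gives no rule for an individual woman whose value is missing.

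**This belongs in the analysis plan.** In part. The detail could sit there, but the article itself states the no-imputation rule and its justification, and the two do not fit the baseline-adjusted models.

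**The gain may be smaller than calculated.** This stands for step count. A woman whose phone records no steps at 30 weeks may lack them at 6 and 12 months too, and keeping her then recovers little. Likewise, with a single missing baseline the indicator absorbs that woman's level and the gain is close to nil.

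**Conclusion.** The point holds in a limited, conditional form. The combination of baseline covariate, no imputation and reliance on maximum likelihood leaves missing baselines uncovered, and any woman affected would leave that outcome's adjusted model despite having follow-up data. At an assumed 5% to 30% missing, 57 down to 42 of 60 women would be used, with an SE about 2% to 14% larger than if all were kept. This rests on r = 0.5, complete follow-up and baselines missing completely at random. At zero missing there is no effect.

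Two stronger readings are tempting and should not be drawn. One is bias between the arms: baseline values are missing or present before allocation, so dropping those women does not in itself unbalance the comparison. The other is damage to the feasibility conclusions: these models give secondary estimates without P values, and the primary feasibility proportions and progression thresholds do not depend on them. What suffers is the precision of those estimates and how well they represent the women randomized. This is a minor point, worth correcting because correction is nearly free.

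**What to change.** Limit the no-imputation rule to post-randomization outcomes. Add one sentence: where a baseline covariate is missing, it is replaced by the overall mean of the observed baselines, pooled over both arms, and a missing indicator is added to the model. Report the number of women in each adjusted model and the number with a filled baseline. If no baseline is missing for an outcome, the indicator is omitted and the planned model is unchanged.

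Do not move baseline into the outcome vector of the planned random-intercept model. That route is acceptable only with an unstructured covariance, because the common-correlation assumption can make the reported confidence intervals too narrow.

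The cost is one sentence in the analysis plan and one extra variable in the model code. No new data are needed.

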## Results

Recruitment and enrollment began in February 2022. Future outcomes will be published in peer-reviewed health-related research journals and presented at national, regional, or state professional meetings and conferences. This publication is based on protocol version 2, January 19, 2022.

## Discussion

### Overall Aim

The overall aim of this RCT is to test the feasibility of undertaking a definitive trial of a diabetes prevention intervention including a smartphone app and group support over 15 months in women with GDM from randomization in the antenatal period to 12 months post partum. Secondary aims are to summarize anthropometric, biomedical, psychological, and lifestyle outcomes overall and by allocation group, and to undertake a process evaluation. Prior to undertaking a definitive RCT of effectiveness, evidence is needed to determine if such a trial could be undertaken and confirm outcomes likely to be of the most importance in a future trial.

### Strengths and Limitations

To our knowledge, this is one of the few feasibility RCTs to test a smartphone app designed to prevent T2D by intervening prior to birth for women with GDM. It is also the first RCT we know of developed specifically for the prevention of T2D for Malaysian women with GDM. Further, the primary ethnic groups in this study (Malay, Chinese, and Indian) are also the major ethnic groups in Asia, and therefore, if this intervention proves to be effective in the larger RCT, this may also be applicable to the wider Asian population. The limitations are that this a feasibility study and therefore not powered to test effectiveness at this stage.

